**01 Background and rationale**

Combined analysis of patient outcome after both external beam radiotherapy (RT) and brachytherapy has recently led to the assumption that the α/β ratio of prostate cancer is lower than for most other tumors and approaches a value characteristic to normal late responding tissues. Values between 1.2 and 4 Gy have been proposed (1-8). Therefore, to deliver an equivalent biological dose (BED) to the prostate using fewer and larger than conventional 2 Gy fractions (hypofractionation), the total dose must be proportionally reduced. If the α/β ratio is lower in the tumor than in the surrounding late responding normal tissues, the equivalent total dose delivered to the former will translate in a significant reduction of the total equivalent 2 Gy dose absorbed by the latter, with a potential decrease in the late side-effects. Hypofractionation would also reduce the acute side-effects providing the overall time would be sufficiently long to allow the repopulation of the early responding normal tissues.

Fraction sizes > 2 Gy have already been used by other groups which reported results that seemed to be comparable to conventional schedules (9-12). These observation were partially confirmed by 2 recent randomized trials on T1-T2 prostate cancer (13,14), which reported similar late toxicity rates between the short and conventional schedule. However, the 5-year biochemical failure rate in the Canadian study (13) was significantly higher in the hypofractionation in comparison to standard fractionation arm (59.95% vs 52.95%), likely because of the non biological equivalence of the 2 schedules (an α/β ratio < 1 should have been used to obtain the equivalence between the shorter and conventional schedule).

Androgen deprivation (AD) has become the standard treatment in combination with RT in high risk tumors, although the duration of AD and the sequence between the two modalities has not yet been optimized (15-18). A recent randomized study (19) showed a superiority of 3-year with respect to 6-month AD in combination with 70 Gy conventional fractionation RT. However, the today standard dose delivered to the prostate is higher than 70 Gy (20) especially in high risk tumors and, therefore, the role and duration of AD should be redefined.

**02 General remarks**

This is a randomized study of hypofractionation vs. conventional fractionation RT in combination with total AD in high risk tumors.

**2.1** *Definition of high risk tumors*

The patients with high risk tumors are those with an iPSA > 20 ng/ml or GS >7, or T-stage >2c, or with the presence of at least 2 of the following clinical factors: iPSA 11-20 ng/ml, T= 2c, GS=7 (20).

**2.2** *Treatment*

The patients will be treated with a short or conventional RT course to prostate and seminal vesicles (SV), no matter of the risk of microscopic N+, in combination with 9-month total AD.

**03 Trial objectives**

**3.1** *Primary objective*

Reduction of late toxicity while maintaining the same Freedom from biochemical failure (FFBF) by hypofractionation with respect to conventional fractionation radiotherapy .

**3.2** *Secondary objective.*

Overall survival, Cause-specific survival, local, regional and distant control.

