**05 Study Design**

This is a phase III, non blinded, randomized study comparing 80 Gy conventional fractionation RT with a biologically equivalent hypofractionated course. The equivalence has been calculated by means of the linear-quadratic model using an α/β ratio of 1.5 as shown by several studies (1,5,6). The aim of this study is to determine if incidence of late toxicity is lower with the hypofractionation than with conventional fractionation, maintaining the same rate of local control/FFBF.

LHRH LHRH LHRH

0 7 67 97 102 123 187 270

Days **--------------------------------------**

Arm B___

Arm A_______

bicalutamide

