**10 Statistical considerations, sample size, data analysis and reporting**

The main objective of the trial is to investigate the late toxicity and freedom from biochemical failure.

This is a single-institution, prospective, phase III randomized trial designed to randomize patients with high risk prostate cancer to receive 80 Gy in 40 fractions in 8 weeks at 2.0 Gy per fraction (arm A, conventional fractionation) or 62 Gy in 20 fractions in 5 weeks (4 fractions per week) at 3.1 Gy per fraction (arm B, hypofractionation) to the prostate. The two arms were hypothesized to be isoeffective with regard to tumor control. However, with regard to late complications, the hypofractionation regime of this trial should be equivalent to 75 Gy given at 2.0 Gy per fraction that is lower than 80 Gy given in the conventional fractionation arm. From the data available in the literature and using the Lyman-Burman-Kutcher (LBK) model the 3-year rates of grade 2 or higher late rectal damage were estimated to be approximately 29% and 12% after 80 or 75 Gy, respectively, delivered at 2.0 Gy per fraction. On the basis of an 80% power to detect a significant difference (p<0.05, two sided), 84 patients were required in each arm (168 patients in total).

Late toxicity and outcome will be analyzed after median follow-up has reached 3 years.

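### The primary objective includes keeping FFBF the same, but the trial is sized only for late rectal toxicity and 84 per arm estimates the FFBF difference only to about ±9 to ±14 points

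*Protocol*

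**What the plan says.** Protocol section 3.1 sets one primary objective with two halves: "Reduction of late toxicity while maintaining the same Freedom from biochemical failure (FFBF) by hypofractionation". Section 05 repeats the second half ("maintaining the same rate of local control/FFBF"), and section 10 opens with "The main objective of the trial is to investigate the late toxicity and freedom from biochemical failure".

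Section 10 contains one sample size calculation. Its endpoint is late rectal damage of grade 2 or higher at 3 years, with modelled rates of 29% and 12%: "On the basis of an 80% power to detect a significant difference (p<0.05, two sided), 84 patients were required in each arm".

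On tumour control, section 10 says only "The two arms were hypothesized to be isoeffective with regard to tumor control". The basis is in section 05: "The equivalence has been calculated by means of the linear-quadratic model using an α/β ratio of 1.5". Section 01 reports proposed α/β values for prostate cancer from 1.2 to 4 Gy.

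The protocol states no FFBF margin, expected FFBF rate, number of events or FFBF power. Toxicity and outcome are to be analysed together once median follow-up reaches 3 years.

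**The concern.** Saying that control is maintained with a different schedule is a non-inferiority claim. It needs a stated tolerable loss and enough patients to rule that loss out. Here the number of patients was fixed on a superiority comparison of a different endpoint, and equal control enters as a modelling premise.

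The protocol itself shows that the premise can fail. Section 01 describes an earlier randomised trial in which 5-year biochemical failure was 59.95% with hypofractionation against 52.95% with standard fractionation, and attributes this to schedules that were not biologically equivalent. A loss of control is thus the main risk to be weighed against lower toxicity. If FFBF turns out not significantly different, a reader of the primary objective could take both halves as met, although the data would be compatible with a considerable loss.

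**Working it through.** **1. The stated sample size.** Inputs from section 10: 29% v 12%, two-sided 0.05, 80% power. The unpooled normal approximation gives n = (1.96 + 0.8416)² × (0.29×0.71 + 0.12×0.88) / 0.17² = 7.849 × 0.3115 / 0.0289 = 84.6 per arm. The stated 84 is reproduced to within one patient, so the toxicity sizing is not in question.

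**2. Is equal control assured by the dose calculation?** Inputs from 7.1 and 7.2: 40 × 2.0 Gy and 20 × 3.1 Gy. The 2-Gy equivalent of arm B is 62 × (3.1 + α/β) / (2 + α/β), without a term for overall time:

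- α/β 1.2: 62 × 4.3 / 3.2 = 83.3 Gy
- α/β 1.5 (the protocol's choice): 62 × 4.6 / 3.5 = 81.5 Gy
- α/β 4: 62 × 7.1 / 6 = 73.4 Gy

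It equals 80 Gy where 62(3.1 + x) = 80(2 + x), so x = 32.2 / 18 = 1.79. Below that value arm B is the higher dose to the tumour, above it the lower. Section 10's late-effect equivalent of 75 Gy corresponds to x = (192.2 − 150) / 13 = 3.25, which lies inside the tumour range given in section 01.

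**3. Precision for FFBF at 84 per arm.** The protocol gives no FFBF rate, so 90%, 80% and 70% are assumed, equal in both arms. SE = √(2p(1−p)/84); the 95% CI half-width is 1.96 × SE. The chance that the interval excludes a deficit m when the true difference is zero is Φ(m/SE − 1.96).

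| Assumed FFBF | SE | Half-width (points) | Excludes 7 | Excludes 10 | Excludes 15 |
|---|---|---|---|---|---|
| 90% | 0.0463 | 9.1 | 33% | 58% | 90% |
| 80% | 0.0617 | 12.1 | 20% | 37% | 68% |
| 70% | 0.0707 | 13.9 | 17% | 29% | 56% |

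The n per arm for 80% power is 2p(1−p) × 7.849 / m². For 7 points it is 289 (FFBF 90%) to 673 (70%), for 10 points 142 to 330, and for 15 points 63 to 147.

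**4. What a non-significant result would mean.** Suppose a true 7-point deficit and a two-sided 0.05 test of the difference. Power is Φ[(0.07√84 − 1.96√(2p̄(1−p̄))) / √(p₁(1−p₁) + p₂(1−p₂))]. For 90% v 83% this is Φ[(0.6416 − 0.9472) / 0.4807] = 26%, so the result is non-significant 74% of the time. For 80% v 73% it is 81%, and for 70% v 63% it is 84%.

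These figures treat FFBF as a simple proportion with complete follow-up. At a median follow-up of 3 years about half the patients have been followed for less than 3 years, and no dropout allowance is stated, so precision at 3 years would be somewhat worse.

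**The case against.** The strongest defence is that toxicity is the tested hypothesis and equal control the design premise. Section 05 asks whether late toxicity is lower, and FFBF follows as a qualifying phrase; section 10 calls the arms hypothesised to be isoeffective. On that reading the fault lies in the wording of 3.1. This has force and shapes the fix, but 3.1 and the first sentence of section 10 still place FFBF alongside toxicity as an objective.

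A separate statistical analysis plan, not seen here, could define how FFBF is tested and reported, so the lack of a named method is not held against the protocol. Such a plan could not, however, make a number of patients set on toxicity adequate for margins up to 10 points.

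The dose argument cuts both ways: at the protocol's chosen 1.5 arm B is at 81.5 Gy, slightly above control. This shows only that equivalence depends on the value chosen.

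The 7-point figure comes from 5-year results in T1-T2 disease. This trial enrols high-risk patients on 9 months of androgen deprivation. It serves here as a yardstick; it is neither a margin nor an expected rate. A 15-point margin would have 90% power if FFBF were 90%, so it would be too strong to say that 84 per arm can support no FFBF claim at all.

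A reader might also infer that the trial will declare the same FFBF whenever p exceeds 0.05. The protocol does not say so: the two-sided 0.05 criterion stands in the sentence that sizes the rectal damage comparison, and no FFBF test is stated. What can be said is that nothing rules that reading out.

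**Conclusion.** The point holds as a mismatch between the objective and the sizing. Half of the stated primary objective has no margin and no sample size basis, and the model that stands in for them gives equal or higher tumour dose in arm B only for α/β up to about 1.79, within a quoted range that runs to 4 Gy.

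At 84 per arm, even truly equal arms would more often than not fail to exclude a 7-point deficit at every assumed rate from 90% to 70%. The same is true of a 10-point deficit, except near the 90% end. A 15-point deficit could be excluded with reasonable probability only if FFBF is high.

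These conclusions rest on the assumed FFBF range, on equal true rates (except for the chance of a non-significant result in step 4, which supposes a true deficit) and on treating FFBF as a fixed proportion. The toxicity comparison is unaffected.

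**What to change.** In sections 3.1, 05 and 10:

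- Make reduction of late rectal toxicity the sole powered primary objective, and state that the 168 patients are sized for it alone.
- Reword FFBF as an estimated outcome, reported as a difference or hazard ratio with its 95% CI.
- State the expected precision: about ±9 to ±14 points for FFBF of 90% to 70%, before allowing for incomplete follow-up.
- State that a non-significant difference will not be taken as evidence of the same FFBF.

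A later FFBF analysis, for instance at 5 years using the 6-monthly PSA tests already scheduled after year 3, is optional. It would add events but would not lift the limit set by 84 per arm.

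The cost is a change of protocol wording. No extra patients or visits are needed and treatment is untouched. The downside is a less favourable stated claim: lower toxicity with FFBF estimated, in place of lower toxicity with FFBF maintained.

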**04 Patient inclusion criteria**

**4.1** *Inclusion criteria*

Patients ≤80 years old, with histologically proven prostate carcinoma

WHO performance status ≤ 2

Any case with high risk tumor (as above defined)

No pelvic nodes > 1cm at the TC or RM evaluation

Previous TURP is allowed provided there is at least 6 weeks interval with the initiation of RT

Written informed consent

**4.2** *Exclusion criteria*

Previous pelvic RT or major surgery (Colo-rectal anastomosys, Total cistectomy, previous prostate surgery other than TURP, etc.)

Ulcerative proctitis

No previous malignant tumors, with the exception of the cutaneous basal cell carcinoma and other tumors cured from ≥ 5 years.

PSA>100 ng/ml.

**05 Study Design**

This is a phase III, non blinded, randomized study comparing 80 Gy conventional fractionation RT with a biologically equivalent hypofractionated course. The equivalence has been calculated by means of the linear-quadratic model using an α/β ratio of 1.5 as shown by several studies (1,5,6). The aim of this study is to determine if incidence of late toxicity is lower with the hypofractionation than with conventional fractionation, maintaining the same rate of local control/FFBF.

LHRH LHRH LHRH

0 7 67 97 102 123 187 270

Days **--------------------------------------**

Arm B___

Arm A_______

bicalutamide

**06 Therapeutic regimens**

**6.1** *Hormonal Therapy*

**6.1.1** *LHRH Analogues:* an LHRH analog depot (preferably Goserelin 10.8 g) will be administered with a subcutaneous injection at days 7, 97 and 187.

**6.1.2** *Antiandrogens:* the non-steroid antiandrogen *bicalutamide* will be orally administered at a daily dose of 50 mg for 270 days beginning at day 0 (7 days before the first LHRH analogue administration).

**6.2** *Radiotherapy*

The radiotherapy treatment will start at day 67 from the beginning of oral bicalutamide (60 days after the first LHRH analogue).

**6.2.1** *Patient data acquisition:* the treatment planning will be based on TC data acquisition. The volumes of interest (VOI) will be delineated on TC slices, taken at a minimum interval of 5 mm.

**6.2.2** *Target volumes:* The clinical target volume **(CTV)** is the prostate plus the entire SV. Planning target volume **(PTV)** = CTV + margin (according to institutional policy):

|  |  | |  | | | |
| --- | --- | --- | --- | --- | --- | --- |
|  |  |  |  |
|  |  |  |  |  |  |  |
|  |  |  |  |  |  |  |
|  |  |  |  |  |  |  |
|  |  |  |  |  |
|  |  |  |  |  |  |  |
|  |  |  |  |  |

**6.2.3** *Delineation of VOI:* The following volumes will be outlined on the planning CT: CTV, PTV, rectum from the inferior margin of the anus to the rectal- sigmoid junction, bladder, femoral heads. For rectum and bladder, where is possible the *wall* will be delineated; if the internal border of the bladder is not evident, a contour of 4 mm will be delineated.

**6.2.4** *Dose prescription:* Dose is specified to the ICRU reference point, positioned at the isocenter and/or close to the PTV center. Minimal and maximal dose to the PTV is 95% to 107% if achievable with respect to normal tissue dose-volume constraints, which have priority over the 95% dose-coverage of the PTV. Minimal dose to the CTV is 95%. Dose distribution and Dose-Volume Histograms must be accurately recorded.

**6.2.5** *Treatment technique:* Patients will receive either 3D-CRT **6.2.6** *Patient treatment position:* Supine. Personalized body-fix device with ankles support

**6.2.7** *Treatment verification:* the verification of the treatment position with respect to the DRR will be done at least twice a week by the individual institutional method (portal imaging, optic, X-ray or ultrasound device).

**07 Randomization**

All patients will receive a total AD for 9-months and will be randomly assigned to one of the following radiotherapy schedules:

**RANDOM**

Standard

80 Gy/40 F/8 wks (5 F/w)

Bicalutamide 50 mg/day

for 270 days

+

Goserelin 10,8 mg every 12 weeks for 3 times

Hypofractionated

62 Gy/20 F/5 wks (4 F/w)

**7.1** *Arm A (Control)*

**7.1.1** *PTV dose:* The PTV will receive a total dose of 80 Gy in 40 consecutive fractions of 2.0 Gy, 1 fraction per day, 5 fractions per week for 8 weeks.

**7.1.2** *Rectum dose:* maximal dose to the rectum should not be > 80 Gy. V70 and V50 (87.5% and 62.5%, respectively of 80 Gy) should not be > 30% and >50%, respectively, of the entire rectal wall.

**7.1.3** *Bladder dose:*V70 and V50 should not be > 50% and > 70%, respectively, of the entire bladder wall.

**7.1.4** *Femoral head dose:* maximal dose absorbed by the femoral heads should not be > 55 Gy (68.7% of 80 Gy).

**7.2** *Arm B (Experimental arm)*

**7.2.1** *PTV Dose:* The PTV will receive a total doseof 62 Gy in 20 fractions of 3.1 Gy, 1 fraction per day, 4 fractions per week, for 5 weeks. According to the linear-quadratic model, this dose should be at least biologically equivalent to that of the control arm, using an α/β = 1.5 Gy (4).

**7.2.2** *Rectum dose:* the maximum dose to the rectal wall should not be > 62 Gy. V54 and V39 (87% and 61%, respectively of 62 Gy) should not be > 30% and > 50% of the entire rectum wall.

**7.2.3** *Bladder dose:* V54 and V39 should not exceed 50% and 70%, respectively, of the entire bladder wall.

**7.2.4** *Femoral head dose:* the maximal dose to the femoral heads should not exceed 42 Gy (68% of 62 Gy).

**08 Evaluation**

**8.1** *Endpoints*

**8.1.1** *Freedom From Biochemical Failure (FFBF):* time interval from the randomization day to the biochemical relapse defined according to the most recent ASTRO Phoenix definition of nadir PSA +2 ng/ml (21).

**8.1.2** *Acute Toxicity:* Acute toxicity will be assessed using the RTOG/EORTC system (22) extended with a few symptoms not mentioned in the RTOG/EORTC acute radiation toxicity scale. Even a single-occasion symptom above baseline will be scored as toxicity. The AUA symptom index for BPH will be used to evaluate obstructive urinary symptoms (23). The AUA form has to be filled in by the patient (see Appendix)

**8.1.3** *Late Toxicity:* Late side effects will be assessed using a modified ("clinical") SOMA/LENT (24), in which side effects that can only be assessed by laboratory/technical investigations are eliminated. The AUA symptom index for BPH will be used to evaluate obstructive urinary symptoms. The AUA forms will be completed by the patient.

**8.1.4** *Disease-Free Survival (DFS):* time interval from the randomization day to the first clinical sign of disease progression.

**8.1.5** *Disease-Specific Survival (DSS):* time interval from the randomization day to the death for disease, with the exclusion of deaths for other diseases.

**8.1.6** *Overall Survival (OS):* time interval from the randomization day to death for any cause.

**8.2** *Timing*

**8.2.1.***Before treatment*

**a.** *Clinical Examinations*

- General examination

- WHO Performance Status (PS)

- Digital rectal examination with the evaluation of tumor diameter.

**b.** *Instrumental Examination*

- TRUS or MR for the evaluation of tumor local extension

- Pelvic CT or MR

- Multiple sextant prostate biopsy for the definition of Gleason Score

- Anorectal endoscopy for the baseline evaluation of the rectal mucosa (see

in the appendix).

- Bone scan

**c.** *Laboratory examinations*

- Baseline PSA determination

- WBC, RBC, and Platelet count, with HG determination

- Serum Testosteron and Dihydrotestosteron determination

- Histology with GS evaluation

**8.2.2** *During the radiotherapy treatment*

Acute toxicity will be assessed:

- at baseline (prior to radiation)

- once a week during radiotherapy

- 1 and 2 months after the end of radiation (where the acute period by definition terminates).

**8.2.3** *During the follow-up period*

**a.** *Instrumental, Clinical and Laboratory Examinations:*

*-* PSA determination every 3 months for 3 years and then every 6 months.

- Testosteron and Dihydrotestosteron determination every 6 months for 3 years.

- DRE every 6 months for 3 years and, then, every 12 months

- TRUS or MR every 6 months until complete tumor clearance.

- Ano-rectal endoscopy every 6 months for 2 years.

- Sextant biopsies 2 years after the end of radiotherapy.

- Evaluation of the late toxicity every 6 months for 3 years, and yearly thereafter.

**8.2.5** *Summary of the examination timing*

|  | Baseline  evaluation | During  RT | Every 3mo.  for 3 yrs, then every 6 mo. | Every 6mo.  for 3 yrs.,  then yearly | At 2 yrs. or for suspected  Progression |
| --- | --- | --- | --- | --- | --- |
| **Clinical** | X |  |  | X |  |
| General | X |  |  | X |  |
| PS | X |  |  | X |  |
| DRE | X | X (RT end) |  | X |  |
| Acute Tox |  | X (weekly) |  |  |  |
| Late Tox |  |  |  | X |  |
|  |  |  |  |  |  |
| **Instrumental** |  |  |  |  |  |
| TRUS/RM | X |  |  | X (till CR) | X |
| Sextant biopsy | X |  |  |  | X |
| Ano-rectal endo | X |  |  | X (for 2 yrs) | X |
| Pelvic CT/MR | X |  |  |  | X |
| Bone scan | X |  |  |  | X |
|  |  |  |  |  |  |
| **Laboratory** |  |  |  |  |  |
| PSA | X | X (baseline)  X (RT end) | X |  | X |
| Histology (GS) | X |  |  |  | X |
| Blood count | X | X (weekly) |  |  |  |
| Testosteron/  dihidrotestosteron | X |  |  | X (for 3 Yrs) |  |

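### Acute toxicity is counted on any single occasion but scored 10 times in arm A and 7 in arm B, which can favour arm B; the schedule table and the late-toxicity baseline also need repair

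*Protocol*

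**What the plan says.** **Scoring rule.** Protocol 8.1.2: "Even a single-occasion symptom above baseline will be scored as toxicity".

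**Timing.** Protocol 8.2.2 asks for acute scoring "at baseline (prior to radiation"), then "once a week during radiotherapy", then "1 and 2 months after the end of radiation (where the acute period by definition terminates").

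**Treatment length.** Arm A (7.1.1) receives "5 fractions per week for 8 weeks". Arm B (7.2.1) receives "4 fractions per week, for 5 weeks".

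**Summary table.** In 8.2.5 the acute row reads "Acute Tox | | X (weekly"). Its baseline cell is empty, and no column covers the first two months after RT.

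**Late toxicity.** Section 8.1.3 uses a modified SOMA/LENT scale plus the AUA index. SOMA/LENT appears neither in the pre-treatment list (8.2.1) nor in the baseline column of 8.2.5. Section 8.1.3 has no counterpart to the above-baseline rule of 8.1.2.

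**Objectives.** The primary objective (3.1) is "Reduction of late toxicity while maintaining the same Freedom from biochemical failure (FFBF"). Acute toxicity is listed as an endpoint in 8.1 but is named in neither 3.1 nor 3.2.

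**The concern.** When one positive scoring is enough, the chance of being counted rises with the number of scorings. The same is true of worst grade, which is a maximum over scorings. Here that number depends on the arm. A symptom that appears in week 6 and clears by week 8 is recorded in arm A. At the same time from RT start it can be missed in arm B.

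The direction matters because the rationale (section 01) expects hypofractionation to lessen acute effects if overall time is long enough. An excess in arm A would be read as support for that, yet part of it could come from the schedule of scoring.

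Two related gaps affect both arms alike. Staff who work from the table would collect no reference value for the above-baseline rule and would skip the two scorings after RT. And without a SOMA/LENT score before treatment, a late event cannot be separated on that scale from a complaint the patient already had.

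**Working it through.** **Inputs.** RT lasts 8 and 5 weeks (7.1.1, 7.2.1). Scoring is weekly on treatment plus two later scorings (8.2.2). There are 84 patients per arm, with planning rates of 29% and 12% (section 10). The protocol gives no per-scoring rate for acute toxicity, so the rates below are assumptions, equal in both arms.

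**1. The plan's own figure.** The only calculation in the protocol concerns late rectal damage. The unpooled two-proportion formula gives n = (1.960 + 0.842)² × (0.29×0.71 + 0.12×0.88) / 0.17² = 84.6 per arm. The stated 84 is therefore reproduced to within rounding. Power at 84 with the pooled test is 78%. Acute toxicity plays no part in this.

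**2. Number of scorings after baseline.**
- By the text: arm A 8 + 2 = 10; arm B 5 + 2 = 7; ratio 1.43.
- By the table: 8 and 5; ratio 1.60.
- Taking a month as about 4.3 weeks, arm B's first scoring after RT falls at 5 + 4.3 ≈ week 9 from RT start. Arm A is scored weekly in weeks 6 to 8.

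**3. Independent scorings.** The chance of ever being scored over k occasions is 1 − (1 − p)^k.

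| p per scoring | Arm A, k = 10 | Arm B, k = 7 | Gap (points) | Two-sided false-positive rate |
|---|---|---|---|---|
| 2% | 18.3% | 13.2% | 5.1 | 0.15 |
| 5% | 40.1% | 30.2% | 10.0 | 0.27 |
| 10% | 65.1% | 52.2% | 13.0 | 0.40 |
| 20% | 89.3% | 79.0% | 10.2 | 0.44 |

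The last column is the rejection probability of a pooled z-test at 0.05 with 84 per arm. On the table's 8 v 5 schedule, p = 5% gives 33.7% v 22.6%.

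**4. Correlated scorings.** Let p vary between patients as a beta distribution with mean m and intraclass correlation ρ, so a = m(1 − ρ)/ρ and b = (1 − m)(1 − ρ)/ρ. The chance of ever being scored is 1 − ∏ (b + j)/(a + b + j), for j = 0 to k − 1. With m = 5% and 10 v 7 scorings:
- ρ = 0.1: 30.0% v 24.1%, gap 5.9 points, false-positive rate 0.14.
- ρ = 0.3: 19.7% v 16.9%, gap 2.8 points, rate 0.075.
- ρ = 0.5 (a = 0.05, b = 0.95): 13.8% v 12.3%, gap 1.5 points, rate 0.059.

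**5. Equal numbers of scorings.** With 7 in each arm and p = 5%, both arms give 30.2%. The artificial gap is zero.

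**6. Late toxicity without a SOMA/LENT baseline.** Suppose a share s of patients in each arm has an unrelated existing complaint that would be scored as an event. The observed rate is then 1 − (1 − rate)(1 − s). The share is an assumption.
- s = 2%: 30.4% v 13.8%, power 74%.
- s = 5%: 32.6% v 16.4%, power 69%.

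The true difference shrinks from 17.0 to 16.7 and 16.2 points. This is dilution, not bias toward an arm.

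**The case against.** **No acute comparison is fixed.** The single-occasion sentence is a recording rule. Acute toxicity is not an objective, section 10 sets no between-arm acute test, and week-by-week prevalence would fit the text equally well. This stands: the distortion arises only if ever-scored incidence or worst grade is compared. A reader might infer that the trial's acute result is biased by 10 points or more whatever is done. The documents do not support that.

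**Independence is the extreme case.** Symptoms in one week predict symptoms in the next, so the larger gaps are an upper range. This stands, and the correlated figures belong beside them.

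**The extra scorings cover extra treatment.** Only arm A is being irradiated in weeks 6 to 8, so more symptoms then may be a true effect of the longer course. This stands in part. The schedule cannot separate that effect from closer observation, because arm B is not observed in those weeks.

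**Timed from the end of RT, the rule is the same for both arms.** Arm A too is unscored between its RT end and its 1-month visit, and timing from RT start has its own imbalance. This is fair, but it does not remove the 10 v 7 count.

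**The table is only a summary.** A reader might infer that its omissions also favour arm B. They do not: they apply to both arms, and 8.2.2 contains the scorings. What remains is a conflict between text and table.

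**Late baselines are partly covered.** AUA belongs to the acute assessment, which is done at baseline. Anorectal endoscopy is required before treatment, and ulcerative proctitis, previous pelvic RT and major surgery are excluded (4.2). This narrows the gap to SOMA/LENT symptoms and probably keeps the affected share small. The protocol nowhere says that existing complaints will be counted as late damage, so that too would be an inference.

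**Conclusion.** The point holds in conditional form. The text yields 10 v 7 post-baseline scorings, with none in arm B from about week 5 to week 9. If ever-scored incidence or worst grade is compared, the imbalance can favour arm B by about 5 to 13 points with independent scorings at equal rates of 2% to 20%, and by about 1.5 points at ICC 0.5 and mean 5%. The direction was the same under every assumption tried, but the size is not known from the protocol, and some arm A excess may be real.

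The conflict between 8.2.2 and 8.2.5 needs no assumption and has no direction. The missing SOMA/LENT baseline could dilute the 29% v 12% comparison. It is not shown to bias that comparison or to invalidate the sample size.

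The acute part is minor. The SOMA/LENT form is worth adding because it serves the powered endpoint at little cost.

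**What to change.** 1. **Acute scoring.** Score both arms at the same times from RT start: baseline, weekly to week 8, then two later times common to both. Compare worst grade over that common window. This adds three brief scorings per arm B patient, and the end of the acute period, now set from the end of RT, would have to be restated to match. If no visits can be added, keep the schedule and add a comparison restricted to matched assessments: weeks 1 to 5 plus the two scorings after RT, 7 in each arm. Because this leaves out arm A's last three weeks of treatment, report it beside the full comparison and not in its place.
2. **Table 8.2.5.** Mark acute toxicity at baseline and add the 1- and 2-month scorings, or whatever times item 1 settles on, so that text and table agree. This is an edit only.
3. **Late toxicity.** Add one SOMA/LENT form before treatment, confirm in the table that AUA is completed then, and report late events as worsening from baseline. This costs one form per patient and no new procedure.
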